## Trial design {8}

C-STICH is a multi-centre, parallel-group randomised controlled superiority trial, open to all maternity sites across the UK. Women are potentially eligible for C-STICH if they are attending antenatal clinics or admitted to obstetric wards in which the reviewing clinician believes that the placement of a cervical cerclage is the most appropriate treatment to prevent a miscarriage or preterm birth. Women will be invited to take part in the C-STICH trial after the decision is made to perform a cervical cerclage procedure providing that they meet the eligibility criteria detailed below.

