#### Maternal

Miscarriage and previable neonatal death (defined as delivery <24 weeks)Stillbirth (defined as intrauterine death ≥24 weeks)Gestation at delivery (in live births ≥ 24 weeks)Gestational age at delivery (in live births ≥ 24 weeks)Gestational age <28/<32/<37 weeks at delivery (in live births ≥24 weeks)Time from conception to onset of spontaneous vaginal delivery (in live births ≥24 weeks)Sepsis (at any time in pregnancy and until 7 days postnatal)Preterm pre-labour rupture of membranes (PPROM)Mode of initiation of labour (spontaneous or induced)Mode of delivery (vaginal, operative vaginal or caesarean)Cerclage placement complications (cervical laceration/bleeding from cervix/ruptured membranes/bladder injury)Cerclage removal complications (cervical tears/need for anaesthetic/difficult to remove)Other maternal complications: vaginal bleeding/steroid use/chorioamnionitis/maternal pyrexia of 38°C (intrapartum/postnatal)/ admission to HDU or ITU (pre/post-delivery)Serious adverse events

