#### Pregnancy Outcome and Maternity Outcome

The Pregnancy Outcome and Maternity Outcome forms (CRF 5, PART A and PART B) should be used to record the primary outcome and secondary maternal outcomes at the conclusion of the pregnancy.

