### Assignment of interventions: allocation

#### Sequence generation {16a}

Participants should be randomised just prior to the cervical cerclage procedure, to minimise the number of withdrawals and protocol violations, but allowing sufficient time for the obstetrician to prepare the sutures for the procedure. Birmingham Clinical Trials Unit provide a bespoke web-based randomisation with telephone back-up. Patients are entered and randomised into the trial by logging into secure online webpage available at www.birmingham.ac.uk/C-STICH. Each GCP-trained researcher eligible to randomise will be provided with a unique username and password. The online randomisation is available 24 h a day, 7 days a week apart from short periods of scheduled maintenance and when there are occasional network interruptions. Alternatively, investigators can make a Freephone telephone call (Tel - [name]) to the randomisation service. This telephone randomisation service is available between 0900 and 1700 h Monday to Friday.

A Randomisation Form (CRF1) should be used to collate the necessary information prior to randomisation. All eligibility criteria and baseline data items on CRF1 will need to be answered before a trial number and allocation can be given. If an essential data item is missing, randomisation will be suspended but can be resumed once the information is available. This will be followed by a confirmatory email sent to the randomising person, local Principal Investigator, and the main research staff member within the centre.

Women will be randomised in a 1:1 ratio to either monofilament or braided suture material. A minimisation algorithm will be used to ensure balance in the treatment allocation by site, indication for cerclage (a history of ≥3 previous midterm losses or premature births (≤28 weeks)/insertion of a cervical suture in a previous pregnancy/a history of mid trimester loss or premature birth with a (current) shortened cervix (≤25mm)/women whom clinicians deem to be at risk of preterm birth either by history or the results of an ultrasound scan), technique planned (with bladder dissection/without bladder dissection), and intention to commence patient on progesterone (yes/no). A “random element” will be included in the algorithm, so that each participant has a probability (unspecified here) of being randomised to the opposite treatment that they would have otherwise received.

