#### Primary analysis

Pregnancy loss will be summarised by treatment arm using frequencies and percentages. A log-binomial model will be used to generate relative risks (and 95% confidence intervals (CI)), adjusting for the minimisation variables. Adjusted risk differences will also be presented (and 95% confidence intervals).

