### Methods for additional analyses (e.g. subgroup analyses) {20b}

#### Secondary analysis

Secondary outcomes which are binary will be analysed as per the primary outcome. Continuous outcomes which are deemed to be normally distributed will be summarised using means and standard deviations and a linear model will be fitted to generate adjusted mean differences (and 95% CIs). Continuous outcomes which are not deemed to be normally distributed will be summarised using medians and interquartile ranges and unadjusted differences in medians will be produced with 95% CIs. Time to event data will be summarised using medians and interquartile ranges. A cox regression model will be fitted to generate adjusted hazard ratios (and 95% CIs) and a Kaplan-Meier plot will be produced to assess the data visually. All analyses will be adjusted for the minimisation variables (where possible).

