A miscarriage, preterm delivery, or neonatal death 48 h after the cerclage procedure will be considered an outcome and not a SAE and should be reported on the pregnancy outcome form. If a site reports an SAE that the Trials Office believes exempt from reporting, clarification will be sought by the Trials Office, with the site asked to review their reasons for reporting. If both parties then agree the SAE is exempt from reporting, the SAE will no longer require processing, though a record of it and the relating correspondence should be kept by both parties. AEs should still be recorded locally in accordance with local practice/SOPs. Reportable SAEs, for both the participant and their baby, from the day of randomisation into the trial, until the defined end of the trial, should be reported to the Trials Office. Whether observed directly or reported by the patient, these must be recorded on CRF 7 within 24 h of the research staff becoming aware of the event. The PI (or nominated investigator (medically qualified doctor) delegated the relevant responsibility on the delegation log) is required to assign causality, signing the SAE form to confirm their assessment. Where an SAE form has been completed by someone other than an investigator, the original SAE form will be required to be countersigned by the Investigator to confirm agreement with the causality. Assessment of causality must be made by an investigator (definition above) according to the definitions in the table below. If an investigator is unavailable, initial reports without causality assessment should be submitted to BCTU by a healthcare professional within 24 h, but must be followed up by medical assessment as soon as possible thereafter, ideally within the following 24 h. If information is missing from the initial SAE report, including ongoing events where there is as yet no end date, the SAE should be followed up until resolution or stabilisation of the event. Follow-up information should ideally be provided on a new SAE Form, using the SAE reference number provided by the BCTU trials team. For all reportable SAEs, the CI or delegate will review the SAE and provide their own assessment of causality. In cases where either the reporting investigator or the CI believes the SAE related the CI or delegate will also perform an expectedness assessment. This expectedness assessment will be based on the clinical judgement/experience of the CI or delegate, with reference where appropriate, to those SAEs listed as expected below. For expectedness assessment purposes, the following will be considered as expected SAEs:

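### The sepsis outcome counts the whole pregnancy, so as written it includes episodes before randomisation and before any suture is in place

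*Protocol article*

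**What the plan says.** The maternal list under Outcomes {12} in the protocol article gives sepsis an explicit window: "Sepsis (at any time in pregnancy and until 7 days postnatal". Both ends are stated; the opening end is the pregnancy itself.

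Entry to the trial comes later. Under Trial design {8}, "Women will be invited to take part in the C-STICH trial after the decision is made to perform a cervical cerclage procedure". Under Sequence generation {16a}, "Participants should be randomised just prior to the cervical cerclage procedure".

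The Pregnancy Outcome and Maternity Outcome forms (CRF 5) "should be used to record the primary outcome and secondary maternal outcomes at the conclusion of the pregnancy". The article gives no start date for the events recorded there.

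On analysis, "Secondary outcomes which are binary will be analysed as per the primary outcome", and for the primary outcome "A log-binomial model will be used to generate relative risks (and 95% confidence intervals (CI)), adjusting for the minimisation variables". Adjusted risk differences are to be presented as well. Sepsis is therefore compared on both the relative and the absolute scale.

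**The concern.** An outcome in a randomised comparison should count events that the allocation could have influenced. A septic episode before randomisation cannot depend on which thread is placed later, yet under this definition it scores as an event. Nothing else in the article removes it: the eligibility criteria do not exclude women who had sepsis earlier in the pregnancy, and no other section restricts the outcome to later episodes.

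Randomisation makes such episodes equally frequent in the two arms in expectation, so they cannot create a false difference. They can mask a real one, by adding the same number of uninformative events to both sides. The trial cultures vaginal swabs and removed sutures, so infection is of interest when the threads are compared, and an understated relative risk for sepsis would be unwelcome.

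**Working it through.** **Is there a figure in the plan to reproduce?** No. The article gives no rate, target effect or power for sepsis. What follows is an illustration on assumed values, unadjusted for the minimisation variables.

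**Inputs from the article.** Allocation is 1:1 and the final target is 2050 women, so about 1025 per arm with no allowance for loss. The relative risk of 0.59 is borrowed from Sample size {14}, where a 41% relative reduction is planned for pregnancy loss (1 − 0.41 = 0.59). It is not a sepsis effect and serves only as a convenient value.

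**Inputs assumed.** The share f of comparator-arm sepsis events that precede randomisation; alternatively, the share q of all women in each arm with sepsis before randomisation, and the comparator risk pC of sepsis after it.

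**Step 1: relative risk in terms of f.** The early events are the same in both arms and only the remainder carries the treatment effect:

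observed RR = f + (1 − f) × true RR

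- f = 5%: 0.05 + 0.95 × 0.59 = 0.61
- f = 10%: 0.10 + 0.90 × 0.59 = 0.63
- f = 20%: 0.20 + 0.80 × 0.59 = 0.67

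At f = 20%, ln(0.672) / ln(0.59) = 0.75, so the log relative risk shrinks by about 25%.

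**Step 2: both effect measures in terms of q.** The observed risk in an arm is q + (1 − q)p, where p is the risk after randomisation. Hence

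- observed RR = [q + (1 − q)pT] / [q + (1 − q)pC], which lies closer to 1 than pT/pC for any q above 0;
- observed risk difference = (1 − q)(pC − pT), which shrinks only by the factor 1 − q.

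With pC = 5% and pT = 0.59 × 5% = 2.95% (two-sided 0.05, 1025 per arm):

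| q | implied f | braided risk | monofilament risk | RR | risk difference (points) | power |
|---|---|---|---|---|---|---|
| 0 | 0 | 5.00% | 2.95% | 0.59 | 2.05 | about 66% |
| 0.25% | 4.8% | 5.24% | 3.19% | 0.61 | 2.04 | about 64% |
| 0.5% | 9.1% | 5.48% | 3.44% | 0.63 | 2.04 | about 61% |
| 1% | 16.8% | 5.95% | 3.92% | 0.66 | 2.03 | about 56% |
| 2% | 29.0% | 6.90% | 4.89% | 0.71 | 2.01 | about 49% |

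Here f = q / [q + (1 − q)pC], so the two steps describe the same dilution.

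**Step 3: sensitivity to the assumed comparator risk.** Over q = 0.25% to 2%, the observed RR runs from 0.62 to 0.76 if pC = 3%, and from 0.60 to 0.67 if pC = 8%. At q = 0 nothing changes. If the true RR is 1, the observed RR is also 1, whatever q is.

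**The case against.** The strongest reply is that one line in a condensed list is being read too literally. The phrase may be meant only to say that antenatal and postnatal episodes both count and when counting stops. The article has obstetric history taken at consent and recorded on CRF 1, while maternal outcomes go on CRF 5, which suggests that history and outcomes are kept apart. The forms, the full protocol and the statistical analysis plan are not shown, and sites may in practice record only later episodes. This stands as a reason not to claim that the data are biased. It does not rescue the definition: the window is stated rather than left open, and a plan or form that followed it would carry the early events into the comparison.

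The reply is also right on size. No rate of sepsis before cerclage is given, the assumed effect is borrowed from another outcome, and the risk difference barely moves.

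Three stronger readings are tempting and are not supported:

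- A reader might see a contradiction with the safety section, where reportable serious adverse events run "from the day of randomisation into the trial, until the defined end of the trial". That window governs reporting to the Trials Office, which has a different purpose, and it also closes at a different time. It shows that a start at randomisation was available, not that the document contradicts itself.
- A reader might extend the point to vaginal bleeding and the other maternal complications. Those items merely lack a start date, which a condensed article may leave to the full documents; pyrexia is already limited to the intrapartum and postnatal periods.
- A reader might take sepsis to be the main maternal infection outcome, or infection to be a leading way in which the threads differ. The article says neither. Chorioamnionitis and pyrexia are also listed, and the stated rationale is prevention of early delivery.

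**Conclusion.** The point holds as a minor correction to one secondary outcome. As written, the sepsis window includes time before allocation, and any events there can only add noise about the effect of the thread. If such events occur and a true difference exists, the relative risk is drawn towards 1 and precision falls, while the risk difference is almost unchanged.

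How far is unknown and may be negligible. The illustrative shift from 0.59 to between 0.61 and 0.67 rests on an assumed true relative risk and on an assumed 5% to 20% of comparator-arm events falling before randomisation; neither is in the article. It would go too far to say that the sepsis comparison is in fact biased, because that depends on how many early episodes there were and on what the forms captured. The primary outcome, pregnancy loss, is not touched.

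**What to change.** Define the outcome as sepsis from randomisation until 7 days postnatal, and classify sepsis earlier in the same pregnancy as baseline data. Starting at randomisation rather than at suture placement keeps the count in line with the intention-to-treat analysis. For women with recorded sepsis, confirm the event date; where the form holds none, ask the site through the monthly queries described under Plans to promote participant retention and complete follow-up {18b}.

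The cost is one line in the outcome definition, a date check on the records with sepsis, and slightly fewer counted events. The article describes recruitment as complete and follow-up as still running, so the check would be partly retrospective. How many records need a query cannot be judged from the article, because it does not show whether sepsis dates are collected.

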#### Neonatal

Early neonatal death (defined as a death within 7 days after delivery)Late neonatal death (defined as a death beyond 7 days and before 28 days after delivery)Birth weight adjusted for gestational age and sex (in live births ≥24 weeks)Small for gestational age and sex (<10th centile, in live births ≥24 weeks)Resuscitation at birth/additional care required (SCBU/NICU/HDU/transitional)/length of stay in additional care (in live births ≥24 weeks)Antibiotics within 72 h/sepsis (clinically diagnosed/proven) (in live births ≥24 weeks)Early neurodevelopmental morbidity (severe abnormality on cranial ultrasound scan) (in live births ≥24 weeks)Respiratory support (ventilation/CPAP)/days on respiratory support (in live births ≥24 weeks)Supplementary oxygen requirements at 36 weeks post menstrual age(in live pre-term births ≥24 weeks, <36 weeks)Necrotising enterocolitis (Bell’s stage 2 or 3) (live pre-term births ≥24 weeks, <37 weeks)Retinopathy of prematurity requiring laser treatment/disabilities/congenital abnormalities (live pre-term births ≥24 weeks, <37 weeks)Serious adverse events

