### Outcomes {12}

C-STICH collects all the outcomes detailed in the core outcome set for preterm birth [4]. The primary outcome measure is pregnancy loss (miscarriage and perinatal mortality, including any stillbirth or neonatal death in the first week of life). A key secondary outcome in the C-STICH trial is time from conception to pregnancy end (any reason). Other maternal and foetal secondary outcomes include:

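### Oxygen at 36 weeks, length of stay and respiratory-support days are defined in live births with no provision for death, so a survival benefit can look neutral or harmful on them

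*Protocol article*

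**What the plan says.** The protocol article, under Outcomes {12}, Neonatal, builds an analysis population into each outcome:

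- Oxygen: the outcome is "Supplementary oxygen requirements at 36 weeks post menstrual age", and with its population it reads "Supplementary oxygen requirements at 36 weeks post menstrual age(in live pre-term births ≥24 weeks, <36 weeks".
- Respiratory support: "days on respiratory support (in live births ≥24 weeks".
- Stay: "length of stay in additional care (in live births ≥24 weeks".

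Death is listed separately. Death in the first week is part of the primary outcome, "pregnancy loss (miscarriage and perinatal mortality, including any stillbirth or neonatal death in the first week of life", and is also a secondary outcome. The only later mortality outcome is "Late neonatal death (defined as a death beyond 7 days and before 28 days after delivery".

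Under Secondary analysis, binary outcomes take the same log-binomial model as the primary outcome and normally distributed continuous outcomes a linear model. For the rest, "Continuous outcomes which are not deemed to be normally distributed will be summarised using medians and interquartile ranges", with unadjusted differences in medians. Neither section mentions a baby who dies before the measurement. The section on sub-group analyses and missing data confines all sensitivity analyses to the primary outcome. Under Baby Outcome, follow-up of a preterm baby ends at the estimated date of delivery or at discharge, whichever is sooner.

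**The concern.** The oxygen definition removes babies born too late to be assessed, but keeps those who die before 36 weeks post-menstrual age. The two day counts keep every live birth from 24 weeks. A baby born at 25 weeks who dies on day 3 is therefore in all three populations. That baby can contribute at most 3 days of stay or support, which reads as a better result than that of a survivor with a long admission.

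This matters here because survival is what the trial tests. The Background section says that monofilament may prevent miscarriage, stillbirth and neonatal death by preventing early delivery, and the assessment of neonatal outcomes is a stated secondary objective. If one suture saves babies who would otherwise have died in the neonatal unit, those babies add oxygen need and days of care to that arm. The deaths they replace add little or nothing to the other arm. A reader of the neonatal results could then take a benefit for a neutral or adverse effect.

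**Working it through.** **Figures available.** The article gives no rate for these neonatal outcomes. The nearest figure is the 41% relative reduction in pregnancy loss in the sample size section, which reproduces: 1 − 11.2/19 = 0.41. Applying it to death before 36 weeks post-menstrual age is an assumption. All other rates below are also assumed, and only the populations come from the article.

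**Oxygen at 36 weeks.** Let d_B and d_M be the proportions dying before 36 weeks (braided, monofilament). Let o be the oxygen rate in babies who survive in either arm, and e the rate in the extra survivors, d_B − d_M. The number of births in the set is held equal in the two arms. Then:

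- Oxygen cases per live birth: B = (1 − d_B)·o and M = (1 − d_B)·o + (d_B − d_M)·e
- (a) Deaths counted as no oxygen: RR = M/B
- (b) Survivors only: RR = [M/(1 − d_M)] / [B/(1 − d_B)]
- (c) Death or oxygen: RR = (M + d_M)/(B + d_B)

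Worked case: d_B = 15%, d_M = 15% × 0.59 = 8.85%, o = 30%, e = 60%.

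- B = 0.85 × 0.30 = 25.5%; M = 25.5% + 6.15% × 0.60 = 29.19%
- (a) 29.19/25.5 = 1.14
- (b) (29.19/91.15)/(25.5/85) = 32.02%/30% = 1.07
- (c) (29.19 + 8.85)/(25.5 + 15) = 38.04/40.5 = 0.94

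| d_B, d_M | o, e | (a) | (b) | (c) |
|---|---|---|---|---|
| 15%, 8.85% | 30%, 60% | 1.14 | 1.07 | 0.94 |
| 15%, 8.85% | 30%, 30% | 1.07 | 1.00 | 0.89 |
| 15%, 10% | 30%, 60% | 1.12 | 1.06 | 0.95 |
| 15%, 10% | 30%, 30% | 1.06 | 1.00 | 0.91 |
| 10%, 5% | 30%, 60% | 1.11 | 1.05 | 0.95 |
| 10%, 5% | 30%, 30% | 1.06 | 1.00 | 0.91 |
| 20/150, 10/150 | 20%, 60% | 32/26 = 1.23 | (32/140)/(26/130) = 1.14 | 42/46 = 0.91 |
| 20/150, 10/150 | 20%, 20% | 28/26 = 1.08 | (28/140)/(26/130) = 1.00 | 38/46 = 0.83 |

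Every row assumes a survival benefit of monofilament and no harm. Reading (a) always points the wrong way. Reading (b) is neutral, or wrong if the extra survivors are sicker. Only (c) keeps the direction throughout.

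**Mean stay.** Assume 5 days for a death, 40 for a survivor, and 40 to 90 for an extra survivor.

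- d_B = 15%: braided 0.15 × 5 + 0.85 × 40 = 34.75 days. Monofilament 0.0885 × 5 + 34 + 0.0615 × 40 = 36.90, or 39.98 with 90 days. Difference 2.15 to 5.23.
- d_B = 10%, d_M = 5%: braided 36.50; monofilament 38.25 to 40.75. Difference 1.75 to 4.25.

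These death rates were chosen for births at 24 to under 36 weeks. In all live births from 24 weeks the rate would be lower and the shift smaller.

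**Median stay.** Suppose every death falls below the median and extra survivors resemble the others. With 15% deaths, the median is the (0.50 − 0.15)/0.85 = 41st percentile of survivors. With 8.85% deaths it is the (0.50 − 0.0885)/0.9115 = 45th. The shift is modest. If more than half of the babies need no additional care or support, both medians are zero and there is no shift.

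**Gap in the mortality outcomes.** A baby born at 25 weeks reaches 36 weeks at (36 − 25) × 7 = 77 days. A death on day 40 lies in the oxygen denominator but in none of the listed mortality outcomes. The gap can arise for births before 32 weeks, because 36 weeks minus 28 days is 32 weeks.

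**The case against.** A reader might infer that the plan scores babies who died as free of oxygen, and hence that these outcomes are biased against monofilament. The article does not support that. It gives populations and model types but no coding rule. A baby who dies on day 3 could equally be treated as missing, and the separate analysis plan may settle the matter. If deaths are excluded and extra survivors need oxygen as often as other survivors, the relative risk is 1.00.

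The direction is also not certain. If monofilament works by delaying delivery, some babies leave the 24 to under 36 week set and others are more mature when born, which would offset the effect. The illustrations hold the set fixed. Their sizes are within noise: 28 versus 26 events of 150 has a 95% confidence interval of about 0.66 to 1.75, and the composite of 38 versus 46 about 0.57 to 1.19. Medians blunt the effect on the day counts. Most of a survival gain would show in the primary outcome and the two neonatal death outcomes. The listed measures belong to the core outcome set that the trial collects, so replacing them would be hard to justify.

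All of this stands, and it limits the size and certainty of the point. The populations, however, are not left to the analysis plan: the article states them, and they include babies who die. For the day counts no coding assumption is needed, since an early death has a low observed value. Setting deaths to missing does not cure the oxygen outcome either, because it compares groups selected by survival. The mortality outcomes do not cover deaths from day 28 onwards, and no sensitivity analysis is planned for these outcomes.

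**Conclusion.** The point holds for three secondary neonatal outcomes and does not touch the primary analysis. As defined, they do not separate a better neonatal course from an early death. Whether deaths are counted as no oxygen or dropped, a survival benefit can appear as no effect or as harm. On the assumed rates the oxygen relative risk is 1.06 to 1.23 in the first case and 1.00 to 1.14 in the second, against 0.83 to 0.95 for death or oxygen. Mean stay is about 1.8 to 5.2 days longer in the arm with fewer deaths, and the effect on medians is smaller and possibly nil.

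These figures show direction, not expected size. They rest on assumed death and oxygen rates, assumed lengths of stay, and equal numbers of births in the set in both arms. The article does not show that babies who died are coded as not needing oxygen, or that a bias against monofilament will occur.

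**What to change.** Keep the listed core outcomes, show them in survivors, and place them beside mortality. Add two analyses:

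1. Death before, or supplementary oxygen at, 36 weeks post-menstrual age, in the same live-birth population and with both components shown. Name this as the comparison between arms to be interpreted.
2. Length of stay and respiratory-support days with death ranked worst, or days alive without additional care or respiratory support, up to a time point within the neonatal follow-up under Baby Outcome. Ranking is the simpler choice: a window that runs to the estimated date of delivery is longer for babies born earlier, so raw days alive would favour early birth.

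First confirm that deaths after day 28 are captured. Follow-up of a preterm baby stops at discharge or the estimated date of delivery, and the article says only that the Baby Outcome form records the baby's status. State also how a baby discharged before 36 weeks is classified for oxygen.

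The cost is a little more analysis work, and composites that are slightly harder to read, which is why the components are shown. Recruitment is complete, so the additions should be dated and made by people who have not seen results by arm.

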## Introduction

### Background and rationale {6a}

Preterm birth (PTB) is one of the major global challenges in obstetrics and neonatology. An early birth puts survivors at risk of serious long-term disabilities and these outcomes pose a significant burden on parents as well as having economic implications on health services. Second trimester miscarriage and preterm birth form a continuum with the underlying cause often multifactorial and complex [1]. Cervical weakness is one cause of late miscarriage and preterm birth; this can be treated by a cervical cerclage.

A cervical cerclage can be performed either with a monofilament or braided suture material; both sutures are routinely used by clinicians [2]. A monofilament suture may be superior at preventing miscarriage, stillbirth and neonatal death through the prevention of early delivery [3].

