#### Baby Outcome

Please use the Baby Outcome form (CRF 6) to record information about the baby’s status. Only complete this form where you recorded a “live birth” on CRF 5, PART A, the Pregnancy Outcome form.

The end of neonatal follow-up will be different for neonates born preterm compared with term.

For preterm neonates (born less than 37 weeks), the end of trial follow-up will be the estimated date of delivery (as confirmed by first trimester ultrasound) or discharge from hospital whichever occurred sooner.

For term neonates (born after 37 weeks), the end of trial follow-up will be 28 days post-delivery or discharge from hospital whichever occurred sooner.

The baby outcome form should be completed at either of the above time points or at discharge from hospital whichever is soonest.

The end of trial for the *mother* will be 28 days post-delivery or death, whichever occurred sooner.

The study will be deemed complete when all participants and their neonates have reached the defined time points.

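### Disabilities and congenital abnormalities are listed under a preterm-only denominator, so this secondary outcome omits term babies and compares arms within a subset the suture is hypothesised to change

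*Protocol article*

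**What the plan says.** Under Outcomes {12}, Neonatal, the article sets a denominator item by item. One item reads "Retinopathy of prematurity requiring laser treatment/disabilities/congenital abnormalities (live pre-term births ≥24 weeks, <37 weeks", closing with a single bracket. Other items in the same list use the wider population of live births at ≥24 weeks, for example "Respiratory support (ventilation/CPAP)/days on respiratory support (in live births ≥24 weeks" and "Early neurodevelopmental morbidity (severe abnormality on cranial ultrasound scan) (in live births ≥24 weeks".

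Background and rationale {6a} gives the hypothesised mechanism: "A monofilament suture may be superior at preventing miscarriage, stillbirth and neonatal death through the prevention of early delivery". The maternal outcome list makes delivery before 37 weeks an outcome in its own right: "Gestational age <28/<32/<37 weeks at delivery (in live births ≥24 weeks".

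On data collection, the Baby Outcome section limits CRF 6 only by live birth: "Only complete this form where you recorded a “live birth” on CRF 5, PART A, the Pregnancy Outcome form". Term babies are followed: "For term neonates (born after 37 weeks), the end of trial follow-up will be 28 days post-delivery or discharge from hospital whichever occurred sooner".

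The adverse event sections name congenital malformations found in the neonatal period as an example of a reportable event, provided it meets the definition of serious. They exempt malformations seen on the mid-trimester scan.

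**The concern.** Retinopathy of prematurity belongs in a preterm denominator. Disabilities and congenital abnormalities do not, because a baby born at term can have either. Placed in the same item, they take on its population, with two consequences.

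First, events in babies born at ≥37 weeks do not count towards this outcome. Second, the arms are compared among babies born preterm, and preterm birth happens after randomisation and is what the suture may prevent. If one suture prevents some preterm births, its preterm group becomes smaller and holds a larger share of babies born early for other reasons. Abnormality could then appear more common with the better suture when there is no true difference.

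Binary secondary outcomes are to be analysed like the primary, by a log-binomial model adjusted for the minimisation variables. Those are baseline variables, so the adjustment does not undo selection that arises later.

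**Working it through.** **1. Scope of the bracket.** The plan gives no figure to reproduce here, so the first check is textual. In "Respiratory support (ventilation/CPAP)/days on respiratory support (in live births ≥24 weeks" the closing bracket plainly covers both parts of a slash-joined item. The same reading of the retinopathy item covers all three of its parts. If the bracket was meant for retinopathy alone, the other two parts have no stated denominator. The line needs correcting on either reading.

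**2. Inputs for an illustration.** The article gives no rate for abnormality or for preterm birth, so all of these are assumptions:
- abnormality in *a* = 3% of babies in both arms (no true effect);
- preterm birth *P* = 30% with braided, and 24% with monofilament where a 20% relative reduction is assumed (0.30 × 0.80);
- *q* = 40% of affected babies born preterm with braided; the monofilament value is varied.

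**3. Formula.** Rate within preterm births = *a* × *q* / *P* in each arm. Apparent risk ratio, monofilament to braided = (*q*_M / *q*_B) × (*P*_B / *P*_M). The bias therefore depends on how far affected babies' preterm risk follows the overall change.

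| Preterm birth, braided v monofilament | Affected babies born preterm | Rate within preterm births | Apparent RR |
|---|---|---|---|
| 30% v 30% | 40% v 40% | 4.0% v 4.0% | 1.00 |
| 30% v 24% | 40% v 32% (proportional) | 4.0% v 4.0% | 1.00 |
| 30% v 24% | 40% v 36% (half response) | 4.0% v 4.5% | 1.13 |
| 30% v 24% | 40% v 40% (no response) | 4.0% v 5.0% | 1.25 |

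Last row: 0.03 × 0.40 = 0.012; 0.012 / 0.30 = 4.0%; 0.012 / 0.24 = 5.0%; 5.0 / 4.0 = 1.25.

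**4. A second model.** Let only unaffected babies respond, with rate = *a* × *q* / [*a* × *q* + (1 − *a*) × *p*], where *p* is the preterm risk in unaffected babies. Take *a* = 2% to 4%, *q* = 50% in both arms, braided *p* = 25% to 45% and a 20% reduction. The apparent RR is 1.23 to 1.24. For example, with *a* = 2% and *p* = 35% v 28%: 0.01 / 0.353 = 2.83% and 0.01 / 0.2844 = 3.52%, ratio 1.24. This model also assumes that affected babies do not respond, so it does not test that assumption.

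**5. Size against noise.** Assume 1000 live births per arm (2050 / 2 = 1025 women). The last row of the table then gives 12 events in 300 braided and 12 in 240 monofilament preterm births. SE of log RR = √(1/12 − 1/300 + 1/12 − 1/240) = 0.399. The 95% interval is 1.25 × exp(±1.96 × 0.399), or 0.57 to 2.73.

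**6. Events left out.** On the same inputs there are 30 affected babies per 1000, of whom 12 are counted and 18 (60%) are not. With all live births as denominator the comparison is 30 v 30 in 1000 each: RR 1.00, SE √(2 × (1/30 − 1/1000)) = 0.254, 95% interval 0.61 to 1.65. Under the second model, 10 to 20 affected term babies per 1000 live births per arm are left out.

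**The case against.** **Term abnormalities are not lost to the trial.** A reader might infer that every abnormality in a term baby goes unrecorded, or that the whole neonatal safety comparison is biased. The documents do not support that. Serious adverse events are a neonatal outcome without a gestation limit, and reporting covers the baby from randomisation to the end of the trial. Serious malformations first identified in term neonates are captured there. The route is partial, because non-serious events and mid-trimester-scan findings fall outside it. The objection stands in so far as the defect belongs to one outcome line.

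**The size comes from the assumption.** The 1.25 requires that affected babies' preterm risk ignores the suture; with a proportional response it is 1.00. A reader might also insert the 41% reduction and obtain 0.30 / 0.177 = 1.69. That 41% is the sample-size target for pregnancy loss, and the article gives no expected reduction in preterm birth. The 60% left out likewise follows from the assumed 40%. This objection stands.

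**The selection argument reaches other outcomes.** Necrotising enterocolitis and supplementary oxygen also use preterm denominators, and live birth at ≥24 weeks is itself determined after randomisation. True. What is particular here is that two conditions not confined to preterm babies share a line with one that is.

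**The article may condense.** The full protocol and analysis plan are not shown and may separate the three parts. That is possible, but the article states a population for this item, and its care over denominators elsewhere in the list makes a literal reading reasonable.

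**Conclusion.** The point holds for one secondary outcome. As printed, disabilities and congenital abnormalities are assessed only in preterm live births, which omits babies born at ≥37 weeks and conditions on an event that the suture is hypothesised to change. The article gives no reason for the restriction; sharing an item with retinopathy is the likely cause.

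The omission of term babies from this outcome follows from the wording and needs no assumption. The bias is conditional. It requires both that the suture changes preterm birth and that affected babies respond less than proportionally. With a 20% reduction and no response in affected babies, the apparent RR is about 1.25, against a 95% interval of roughly 0.57 to 2.73 on the assumed counts. The likelier practical harm is an incomplete and hard-to-interpret comparison rather than a demonstrably false signal. The primary outcome, the sample size and the key secondary outcome are unaffected.

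A reader might also infer that the term data are already in hand. The article says only that CRF 6 is completed for every live birth and records information about the baby. It does not list the fields, so this remains to be checked.

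**What to change.** Split the item. Keep retinopathy of prematurity requiring laser treatment in live births at 24 to <37 weeks. Report disabilities and congenital abnormalities separately in all live births at ≥24 weeks, the population that the list already uses for its general neonatal outcomes. Give the counts over all women randomised, by arm, alongside. The wider denominator reduces the selection without removing it, because survival to a live birth at ≥24 weeks also follows randomisation; the counts over all randomised let the reader see this.

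Before making the change, confirm that CRF 6 records both items for term babies. If it does, the cost is one line in the outcome list or analysis plan and one extra table row, with no new visits. If it does not, state that term data are limited to serious adverse event reports and label the preterm-only result as descriptive. The article describes the trial as still in follow-up, so the change should be dated and made before the comparative data are seen.
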